### The Aim and Objectives

The aim of the study was to define the role of PLMS in cSVD progression and related cognitive decline progression.

The main objectives of the study are:

1) Assessment of the cognitive function in small vessel disease patients at baseline and in the 2-year follow-up.2) Assessment of MRI markers of cSVD at baseline and in the 2-year follow-up.3) Assessment of sleep quality and health-related quality of life in patients with PLMS in comparison with those without PLMS.4) Evaluation of PLMS impact on cSVD progression through constructing multiple regression model.5) Assessment of the association between PLMS and poor sleep quality based on questionnaire data.

## Methods and Design

### Protocol Outline

This study was designed as a prospective observational study. It will be conducted in Moscow, Russia (Department of Neurology, I.M. Sechenov First Moscow State Medical University).

In-patients aged 60–75 diagnosed with cSVD according to current diagnostic criteria and neuroimaging standards (51, 54) will be evaluated for MRI markers of cSVD and cognitive function over a period of 2 years. General assessment of risk factors for cardiovascular disease will include identification of hypertension (office measured off medication conventional blood pressure of at least 140/90 mmHg), measuring total cholesterol level, calculation of body mass index, as well as revealing by self-report and exploring the medical history the presence of ischemic heart disease, diabetes, and heart rhythm disturbances. Additionally, the duration of smoking and habitual alcohol consumption will be assessed. For the latter purpose, a validated Russian version of the Alcohol Use Disorders Identification Test (AUDIT) will be applied (58).

The design of the study is schematically depicted in Figure 1. All enrolled patients will undergo overnight PSG at baseline. Based on PLMI, all patients will be divided into the experimental (PLMI ≥15/h) and control groups (PLMI <15/h). The assessment of the night sleep and quality of daytime functioning will be made at baseline only. Assessment of cognitive function and brain MRI will take place at weeks 0 (baseline) and 104 (2-year follow-up). The details on the applied study techniques and evaluation of night sleep, cognitive function, and MRI are given in parts 2.4, 2.5, and 2.6, respectively. The examination protocol is resumed in Table 1.

**Figure 1 F1:**
[figure not shown]
Design of the study.

**Table 1 T1:** Examination protocol.

**Methods**	**Baseline**	**2-years follow-up**	**Unit of measurement**	**Range**
Polysomnography	TST	None	Min	Not defined
	SOL	None	Min	Not defined
	WASO	None	Min	Not defined
	SE	None	%	0–100
	AHI	None	Number per hour	Not defined
	LMs	None	Number during the sleep	Not defined
	LMI	None	Number per hour	Not defined
	PLMI	None	Number per hour	Not defined
	PI	None	None	0–1
	SILMS index	None	Number per hour	Not defined
	PLMWI	None	Number per hour	Not defined
	PLMAI	None	Number per hour	Not defined
Questionnaires	AUDIT	None	Points	0–40
	PSQI	None	Points	0–21
	ESS	None	Points	4–24
	GDS	None	Points	0–30
	EQ-VAS	None	Points	0–100
	ISI	None	Points	0–28
Cognitive assessment	MoCA score	MoCA score, percentage change	Points, %	0–30
	12 word test total score	12 word test total score, percentage change	Points, %	0–24
	BVRT score	BVRT score, percentage change	Points, %	0–10
	FAB score	FAB score, percentage change	Points, %	0–18
	TMT-A time	TMT-A time, percentage change	sec, %	Not defined
	TMT-B time	TMT-B time, percentage change	sec, %	Not defined
	B/A ratio	B/A ratio, percentage change	None, %	Not defined
	SDMT score	SDMT score, percentage change	points, %	not defined
	PVFT	PVFT, percentage change	Words, %	Not defined
	SVFT	SVFT, percentage change	Words, %	Not defined
Brain MRI	WMH volume	WMH volume, percentage change	ml, %	Not defined
	Fazekas Scale	Fazekas Scale, percentage change	points, %	0–6
	Scheltens Scale	Scheltens Scale, percentage change	points, %	0–84
	cSVD Scale	cSVD Scale, percentage change	points, %	0–4
	None	Rotterdam progression scale	Points	From −7 to +7

*BVRT, Benton Visual Retention Test; B/A ratio, TMT B time divided to TMT A time; PVFT, Phonemic Verbal Fluency Test; SVFT, Semantic Verbal Fluency Test*.

### Participants

Patients diagnosed with cSVD will be recruited among in-hospital patients (1st and 2nd Department of Neurology, University Clinic 3, Sechenov First Moscow State Medical University, Moscow). According to the Standards for Reporting Vascular Changes on Neuroimaging released in 2013, the neuroimaging characteristics of cSVD consist of WMH, recent small subcortical infarct, cerebral microbleeds, perivascular space, lacune of presumed vascular origin, and brain atrophy (4). The brain MRI of the patient will be assessed by trained radiologist.

Potential participants will be screened for eligibility criteria.

#### Inclusion Criteria

Age between 60 and 75 years.Diagnosis of a cSVD—made on the basis of MRI and clinical features, according to current neuroimaging standards for research into small vessel disease (4) and current diagnostic criteria (7).Ability to follow the procedures of the study, fluent in Russian language—assessed by self-report.

#### Non-inclusion Criteria

History of symptomatic stroke, brain tumor, or traumatic brain injury—assessed by clinical history.Hypothyroidism, B12 deficiency, HIV/AIDS, neurosyphilis, autoimmune, and connective tissue diseases—assessed by clinical history.

#### Exclusion Criteria

History of psychiatric comorbidities and substance use disorder—assessed by self-report, clinical history, and the AUDIT.Significant vision loss (leading to difficulties with performing cognitive tasks)—assessed by self-report and clinical history.Presence of dementia—assessed by history and clinical examination.Movement disorders (e.g., tremor, dystonia) that slow down the speed of performing cognitive tasks—assessed by clinical examination.Obstructive sleep apnea syndrome—according to the criteria of International Classification of Sleep Disorders III (14).Restless legs syndrome—according to the criteria of the International Restless Legs Syndrome Study Group (63).Current intake of neuroleptics, benzodiazepines, selective serotonin reuptake inhibitors, and hypnotics—assessed by self-report and clinical history.

Before recruitment, the MDs will explain to each participant the aim and nature of the study, the main steps to be undertaken, the expected duration, the potential risks and benefits and any discomfort it may lead to, voluntary participation, withdrawal from the study at any time, and that withdrawal of consent will not affect his or her subsequent medical assistance and treatment. After eligibility assessment, potential participants will receive an information paper and a consent form. The consent form will be signed before any study procedures begin. The informed consent (IC) is compiled in accordance with the National Standard of the Russian Federation for Clinical investigations and good clinical practice (GOST R ISO 14155-2014) for the creation of IC for information transfer (64). The protocol of the study and the content of the IC have been approved by the local ethics committee of the I.M. Sechenov Moscow Medical University (no. 15-19/25.11.2019). The study has been registered in ClinicalTrials.gov Protocol Registration and Results System (Identifier: NCT04569643 29.09.2020). The scheduled time for patient recruitment is September 2021 to September 2024. This period will be extended if necessary.

The patients responding to the criteria of inclusion without conditions listed in part 2.2.2 will undergo the routine general clinical assessment and study procedures (nocturnal PSG, neuropsychological assessment, and brain MRI). Patients with identified apnea/hypopnea index (AHI) equal to or more than 5 will be excluded, as well as subjects with conditions mentioned in part 2.2.3. All enrolled patients will be given recommendation according to 2019 American College of Cardiology/American Heart Association Guideline on the Primary Prevention of Cardiovascular Disease (65) for the purpose to manage generally recognized risk factors for cardiovascular disease.

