### Pathophysiology and Cardiovascular Effects of PLMS

Initially, PLMS were studied in close connection with RLS. These conditions are supposed to share common pathophysiological mechanisms since E. Lugaresi et al. showed that most RLS patients had periodic leg movements during sleep (23, 24). RLS is defined by the International Classification of Sleep Disorders (III Edition) as the syndrome characterized by an urge to move the legs, sometimes accompanied by an uncomfortable sensation that occurs primarily with rest/inactivity; it is partially or totally relieved by movement, for as long as the movement occurs, and occurs primarily in the evening or at night (14). Despite close relations between PLMS and RLS, they are considered to be different neurological processes since one of them can occur in the absence of the other (23), although the precise origin of PLMD and RLS is not established. Probably, dopamine or its derivatives play the primary role in these states because a high prevalence of both RLS and PLMS is observed in Parkinson's disease patients (25). Moreover, worsening of symptoms is observed after dopamine antagonist intake and vice versa; remarkable improvement can be achieved by dopaminergic agent intake (26). On the other hand, Manconi et al. investigated the role of dopamine using pharmacological agents and revealed that RLS can be reduced using both dopaminergic and non-dopaminergic agents, whereas PLMS respond to dopaminergic agents only (27). Thereby it is likely, that PLMS is under stronger dopaminergic control in comparison with RLS.

The dysfunction of descending inhibitory pathways with subsequent disinhibition of the segmental apparatus of the spinal cord is believed to be the reason for PLMS (28). The D2 and D3 receptors on the preganglionic neurons of the lateral horns are considered to be involved (29). Probably, the diencephalic dopaminergic structures (A11 neuronal group) take part in the genesis of PLMS and RLS because the A11 diencephalospinal pathway is crucial for pain control and sensorimotor integration at the spinal level (30). For example, the study on rats showed the presence of A11 dopaminergic terminals in posterior spinal horns and their vicinity to the motor neurons of anterior horns (31). The model involving the crucial role of dopamine could explain the positive effect of intake of dopaminergic agents in patients with both PLMS and RLS.

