Movements with a duration equal to or more than 0.5 s are regarded as leg movements during the sleep (LMs), and those with a duration of <10 s are candidate LMs (68). Two to four unilateral candidate LMs from the two legs overlapping each other within 0.5-s interval are referred to as one bilateral candidate LM if the total duration is <15 s. The PLMS are defined as candidate LMs series of four or more, separated by more than 5 and <90 s and not interrupted by LM > 10 s (68, 69). The total number of LMs during the sleep will be divided by TST to obtain LMI. The PLMI will be calculated as the number of PLMS per hour of sleep (70). Periodic limb movements during wakefulness (PLMW) are movements that meet the criteria of PLMS but occur during bedtime when patient is awake. PLMAI is a number of associations of PLMS series with EEG arousals per hour of sleep (71). The number of PLMW per hour of wakefulness during bedtime is PLMW index. The number of intermovement intervals that will be 10–90 s long and all in sequences of at least three will be divided by the total number of intervals to calculate the PI (70, 72). This index lies within 0 (absence of periodicity) to 1 (complete periodicity). Total number of doublets of LMs with intermovement interval <10 s is divided by TST to gain SILMS index (73). Experimental and control groups will be formed based on PLMI. The experimental group will include patients with PLMI ≥ 15/h, and the control group will include subjects with PLMI <15/h.

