## Discussion

PLMS are regarded as the possible sign of repetitive autonomic dysfunction during night sleep. Nevertheless, it is not known if this autonomic dysfunction can worsen the course of cardiovascular pathology, as well as increase the risk of cardiovascular events. In this regard, the investigation of the long-term effects of PLMS seems to be worth researching.

The proposed protocol of the study allows estimate influence of PLMS on both the course of cSVD and incidence of stroke. WMH increase and cognitive decline, which are the key features of cSVD progression, will be assessed. In comparison with the researches conducted by Kang et al. (51) and Del Brutto et al. (105), our study has a longitudinal observational design, which seems to be more appropriate for the purpose of risk factors identification than a cross-sectional design. These researchers came to the opposite conclusions in their studies that seem to support the utility of further investigation of the problem. Besides, the proposed protocol suggests a more detailed MRI assessment. Estimation of different brain regions separately is another strength of our study.

In comparison with another prototype study conducted by Leng et al. (54), the proposed study has also some strengths. The neuropsychological examination is more detailed and comprehensive. Particular attention is paid to the assessment of executive functions since they are affected by vascular cognitive impairment to a greater extent.

The results of the proposed research have potential practical value because PLMS is a treatable condition. If PLMS is identified as a predictor for cSVD progression, it could be regarded as a modifiable risk factor for cSVD, which can be managed. Eventually, it may contribute to improving patient outcomes.

Several limitations of the study should be considered. The design of the study does not allow to reveal the exact mechanism of how PLMS leads to cSVD progression and cognitive decline. If the hypothesis of the research is confirmed, we will be able to assume the possible underlying process only. Finally, because of the short follow-up period, no differences between groups might be yielded and the role of PLMS can be underestimated.

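### The drug exclusions omit dopaminergic agents, the one class the protocol says PLMS respond to, so a treated PLMS patient can be classed as a control

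*Protocol article*

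**What the plan says.** The Exclusion Criteria list the drug exclusions item by item: "Current intake of neuroleptics, benzodiazepines, selective serotonin reuptake inhibitors, and hypnotics", established from the patient's own report and the clinical history. Dopaminergic agents are not on the list.

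The section on pathophysiology and cardiovascular effects describes the effect of these agents on the condition under study. After noting that dopamine antagonists make symptoms worse, it says that "remarkable improvement can be achieved by dopaminergic agent intake". It then reports a pharmacological study in which restless legs syndrome (RLS) responded to several kinds of agent, "whereas PLMS respond to dopaminergic agents only". The Discussion adds that "PLMS is a treatable condition".

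Under Nocturnal PSG, group membership follows from the measured index alone: "The experimental group will include patients with PLMI ≥ 15/h, and the control group will include subjects with PLMI <15/h". The Protocol Outline says of the sleep measurements: "The assessment of the night sleep and quality of daytime functioning will be made at baseline only". Table 1 accordingly shows no polysomnography value at two years. The adjustment set in the statistical section has seven cardiovascular covariates and no drug term.

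**The concern.** PLMI is the exposure. It forms the two groups and is the tested predictor in the regression. A drug that lowers PLMI on the night of recording changes the measured exposure, but it does not undo exposure that occurred before the drug was started.

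The list also screens in one direction only. Neuroleptics, which act against dopamine and by the protocol's account would worsen symptoms, are excluded. Drugs that the protocol says reduce PLMS are not.

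What is at stake is attenuation. If suppressed patients still carry some raised risk of progression, placing them among controls brings the control mean closer to the PLMS mean. The Discussion already warns of a possible null result and puts it down to short follow-up. Misclassified controls would be a second explanation that could have been prevented.

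**Working it through.** **Step 1. Apply the written rules.** Take a patient of 60 to 75 with cSVD, no RLS, no movement disorder that slows testing, an apnea/hypopnea index below 5, and current dopaminergic intake. No printed criterion removes this patient. If the drug holds PLMI below 15/h at the baseline recording, the patient is a control. No listed covariate distinguishes this patient from a control who never had PLMS.

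**Step 2. Share of controls affected.** Inputs:
- Prevalence of PLMS above age 60: 34% (Background). This is a general figure; the protocol says prevalence in cSVD has not been evaluated.
- Share k of true cases suppressed at the recording: not in the documents. Assumed 2%, 5% and 10%.

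Formula: f = 0.34k / (0.66 + 0.34k)

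- k = 2%: 0.0068 / 0.6668 = 1.0%
- k = 5%: 0.0170 / 0.6770 = 2.5%
- k = 10%: 0.0340 / 0.6940 = 4.9%

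In a control group of 49 that is about 0.5, 1.2 and 2.4 patients.

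**Step 3. Effect on the difference.** Let r be the share of the excess progression that suppressed patients keep. The control mean rises by f × r × (true difference), so the observed difference is the true difference × (1 − f × r).

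- r = 1 (they progress like untreated cases, the worst case): the difference shrinks by 1.0%, 2.5% or 4.9%.
- r = 0.5 and k = 10%: 0.049 × 0.5, about 2.4%.
- r = 0 (treatment removes all excess risk): no shrinkage.

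**Step 4. Effect on power.** The protocol's figure for the two-group comparison is 49 per group (effect size 0.5, α = 0.05, β = 0.2). Read as a standardised effect with the one-sided alternative stated under Hypothesis, 2 × ((1.645 + 0.842) / 0.5)² = 49.46. That rounds up to 50, one above the stated number. Other readings give larger groups: 63 for a two-sided standardised effect of 0.5, and 74 (one-sided) or 94 (two-sided) for a raw difference of 0.5 with SD 1.22. The 49 serves here only as a base for illustration.

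Worst case (r = 1), 49 per group, one-sided, normal approximation:

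| k | effect size 0.5 × (1 − f) | power | per group for 80% |
|---|---|---|---|
| 0 | 0.500 | 79.7% | 50 |
| 2% | 0.495 | 79.0% | 51 |
| 5% | 0.487 | 77.9% | 53 |
| 10% | 0.476 | 76.1% | 55 |

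**Step 5. Regression.** For the same patients the recorded PLMI lies below the level of their earlier exposure. If past exposure still drives progression, the coefficient is distorted in the same way. The documents do not allow this to be quantified.

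**The case against.** The strongest case on the other side has four parts.

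- **Few users are likely.** RLS, which the protocol calls the closest association of PLMS, is excluded, and so are movement disorders that slow cognitive tasks. This stands, and it is why the assumed range stops at 10%. It narrows the gap without closing it: the Background links PLMS to Parkinson's disease, and a patient whose disorder does not slow testing stays eligible.
- **A suppressed patient may belong among the controls.** The proposed mechanism is sympathetic activation accompanying the movements, and the protocol reports a view that it is absent without them. On that view a treated patient is currently unexposed. This stands as a condition: attenuation arises only so far as risk from earlier exposure persists.
- **Drug use may well be recorded.** A reader might infer from the article that dopaminergic intake is never captured. The documents do not support that. The article mentions a routine clinical assessment and the medical history, and a medication form is a detail that a condensed article commonly leaves to the full protocol.
- **Treatment begun after baseline is conjecture.** A reader might infer that patients with high PLMI will be treated during the two years and dilute the effect unseen. Nothing shows that a high PLMI leads to drug treatment here. The Rationale leaves pharmacological correction to future studies, and the advice described for enrolled patients concerns cardiovascular risk factors.

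**Conclusion.** The point holds for eligibility and classification at baseline. The printed list omits the one drug class that the protocol says PLMS respond to, and a single recording then fixes the groups. As written, the rule can place suppressed PLMS patients among controls.

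The consequence is conditional and probably small. With 2% to 10% of true cases suppressed and 34% prevalence, both taken as assumptions for this sample, about 1% to 5% of controls are affected. In the worst case power falls from 79.7% to between 79.0% and 76.1%. If treatment removes the excess risk, the bias disappears. It would therefore be wrong to read the point as a certain loss in proportion to f.

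**What to change.** Do one of the following at baseline:

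1. Handle dopaminergic intake at the baseline polysomnography as the four listed classes are handled, by the same self-report and clinical history; or
2. Record that intake and prespecify a sensitivity analysis of the primary comparison (percentage change in total WMH volume) without baseline users.

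In either case, ask about intake at the existing week-104 visit and report it descriptively by group. Excluding patients who started such a drug after baseline should not become a main analysis: that selects on a post-baseline event which may itself follow from a high PLMI or its symptoms.

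The cost is one item in the eligibility list or medication record, one question at a visit already planned and, under the second option, one extra analysis. Under the first option a few otherwise eligible patients are lost. Neither option asks anyone to start, stop or change a treatment.

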### Nocturnal PSG

Participants will undergo nocturnal stationary PSG (SOMNOscreen™, SOMNOmedics GmbH, Germany) at baseline. The PSG protocol will include electroencephalography (EEG) with registration of six monopolar recordings (Fp1A2, Fp2A1, C3A2, C4A1, O1A2, and O2A1); two electrooculography (EOG) channels; one electromyography (EMG) channel for chin muscles; two EMG channels for right and left tibialis anterior muscles; electrocardiography (ECG); recording of chest and abdominal movements, respiratory flow signal, blood oxygen saturation, and snoring; and registration of body position. Synchronized video recording will be made. Trained somnologist will analyze the data manually in accordance with criteria of The American Association of Sleep Medicine Manual for the scoring the sleep and associated events, version 2.6 (2020) (66). SOMNOwatch software “DOMINO® version 2.9.0” (SOMNOmedics GmbH, Germany) will be used for processing of records.

Sleep parameters will be calculated taking into account rules for recording and scoring periodic leg movements in sleep and wakefulness determined by the International Restless Legs Syndrome Study Group in 2006 (67) and then revised in 2016 (68). Following values will be obtained: total sleep time (TST), sleep-onset latency (SOL), wake after sleep onset (WASO), sleep efficiency (SE; percentage TST of time in bed), AHI, total number of LMs, number of LM per hour of sleep LM index (LMI), PLMI, index of periodic limb movements with arousals within 3 s of movement termination (PLMAI), periodic limb movements of wakefulness index (PLMWI), periodicity index (PI), and short-interval leg movements index (SILMS index).

Patients with obstructive AHI (equal to or more than five episodes per hour of sleep) will be excluded from the study and will be given recommendations for following examination and treatment.

Movements with a duration equal to or more than 0.5 s are regarded as leg movements during the sleep (LMs), and those with a duration of <10 s are candidate LMs (68). Two to four unilateral candidate LMs from the two legs overlapping each other within 0.5-s interval are referred to as one bilateral candidate LM if the total duration is <15 s. The PLMS are defined as candidate LMs series of four or more, separated by more than 5 and <90 s and not interrupted by LM > 10 s (68, 69). The total number of LMs during the sleep will be divided by TST to obtain LMI. The PLMI will be calculated as the number of PLMS per hour of sleep (70). Periodic limb movements during wakefulness (PLMW) are movements that meet the criteria of PLMS but occur during bedtime when patient is awake. PLMAI is a number of associations of PLMS series with EEG arousals per hour of sleep (71). The number of PLMW per hour of wakefulness during bedtime is PLMW index. The number of intermovement intervals that will be 10–90 s long and all in sequences of at least three will be divided by the total number of intervals to calculate the PI (70, 72). This index lies within 0 (absence of periodicity) to 1 (complete periodicity). Total number of doublets of LMs with intermovement interval <10 s is divided by TST to gain SILMS index (73). Experimental and control groups will be formed based on PLMI. The experimental group will include patients with PLMI ≥ 15/h, and the control group will include subjects with PLMI <15/h.

